## Aim 2: development of e-mental health interventions

### Involvement of affected persons and their relatives

Persons affected by suicidality and relatives of suicidal persons are involved during the whole developmental process of the e-mental health interventions. In German-speaking countries the term “trialogic” or “trialogue” describes the exchange between persons affected by a health problem, relatives/close persons (e.g. friends, family members), and professionals [48–50]. Recruitment was done via the trialogic assembly *“Irre menschlich Hamburg e.V.”* [51, 52]. This lived experience team reviews all text materials in a structured process before its online release. In the interactive online intervention, the lived experience team contributes digital postcard messages, written experience reports, and videos in which they share their personal experience regarding suicide (personal stories).

Members of the lived experience team are at least 18 years old, are given a Participant Information Form, and provide informed consent. Members decide the extent of their participation and have the right to revoke their participation in the project at any time (including the provision of the video and text material).

### Development of evidence-based health information

The method of developing evidence-based health information conforms to international and national [53] quality criteria for the creation of online health information and decision guidance. A methodological paper is developed on this basis and comprises the following aspects [54]:Sources are national [55] and international [56] guidelines and systematic reviews.During the development and evaluation of the material, persons affected by suicidality participate through the collaborative involvement of self-help organisations, trialogic organisations or patient associations.Fact sheets include the development date and the date for the next revision. All information is reviewed at least once a year and revised if required.All persons involved in the development of health information are advised to represent only the interests of their delegating organization.Experts in the specific area are involved in content development. The authors of a text and their qualifications are named. Experts, and members of the lived experience team assess the text material in a structured peer-review process.

In developing the e-mental health interventions we also consider media guidelines for suicide reporting [57]. Evidence-based health information on suicidality is used for the extension of https://www.psychenet.de/ as well as for the interactive online intervention.

### Development of the interactive online intervention

The interactive online intervention has been developed on the basis of the design, lessons and evidence from the existing Australian project *The Ripple Effect* [31, 40]—an intervention with a focus on rural farming populations. The current intervention content has been translated and adapted to the German cultural context and the focus has been broadened to a general population sample [31].

The project team of *The Ripple Effect* has provided advice on the development of the current intervention. A close collaboration (skype conferences, multi-day face-to-face workshop) with the Australian team has been conducted to build on their groundwork and experience when developing and evaluating the interactive online intervention.

A web design agency is responsible for technical implementation and the design of the intervention. Responsive design, which makes the intervention render well on a variety of devices, like smartphones or tablets, will be applied to enhance user-friendliness.

### Content of the interactive online intervention

The interactive online intervention consists of five chapters (as described in Table 1). A combination of core content and optional content allows participants to choose the level of detailed information preferred.

**Table 1 Tab1:** Content of the interactive online intervention

Chapter 1: Psychoeducation	
- Evidence-based health information: meaning of suicide respectively suicidality, frequency of suicide, possible causes of suicidality, warning signs, precipitating events, risk- and protective factors	
- Werther- and Papageno effect	
- Suicidality as a continuum	
- Suicide taboo: meaning and function of a taboo in general and for suicide in particular, reasons for tabooing suicide	
- Suicide stigma: meaning of stigma and stigmatization in general and concerning persons with experience of suicide, self-stigma, suicidality as consequence of stigmatization, difference between experienced and anticipated stigmatization, suicidality in various situations (migration background, serious physical dieseases, higher age, homosexual or bisexual orientation, transgender)	
- Selected results of the representative population survey	
- Falsities concerning suicidality opposed to reality	
Chapter 2: Experience reports on suicidality	
- Video reports and text messages by persons with an experience of suicide: e.g. understanding suicide attempts or thoughts, helpful strategies to deal with suicidality from the perspective of affected persons (e.g. “What helped me to deal with suicidal thoughts?”; “What helped me to deal with the suicide of a close person?”)	
Chapter 3: Strategies I - Behavior, Body, Mind, Feelings	
Strategies to deal with suicidality or stigmatization:	
- Explaination of the link between behavior, body, thoughts and feelings	
- Behavior: link between activity and well-being, creating a personal list of positive activities	
- Body: Progressive muscle relaxation	
- Mind: cognitive restructuring technique, questioning stigma related thoughts	
- Feelings: Psychoeducation about feelings, feelings connected with stigma, Mindfulness technique	
Chapter 4: Strategies II - Communication	
- How to talk about suicidality: communication tips	
Chapter 5: Personal goal setting	
- Personal goal setting according to “SMART” criteria (specific, measurable, agreed, realistic, and time specific). Three personal goals can be set.	

Content of the interactive online intervention is tailored for all five chapters depending on the participant’s experience of suicide: suicide attempt in the past, having suicidal thoughts, having lost a close person by suicide, fearing the loss of a close person by suicide, or interested in the topic in general. For example, a participant of the online intervention who lost someone by suicide will be presented with different communication tips (chapter 4) than a participant who fears losing someone by suicide.

Referral to external support services will be provided via online links and telephone numbers of national and regional services, crisis lines and locations of emergency mental health services. Information on support services will be available from every page of the online intervention.

From chapter 2, participants in the interactive online intervention will be able to read and/or write digital postcard messages about individual experiences of suicide and leave a message to other participants. The digital postcard messages will be screened before being included in the online intervention to ensure they comply with media guidelines for talking about suicide [57].

Participants can successively work on five chapters of the interactive online intervention and divide their time as prefered. Overall, an estimated time of 1.5–3 h will be required to complete the intervention. Participants can pause at any time and continue working at the point where they left off. The period over which participants can work on the intervention is flexible, with an approximate guideline of two to four weeks being recommended.

## Aim 3: evaluation of the e-mental health interventions

### Web analytics

Web analytics tool Matomo (https://matomo.org/) will be used to record data including number of visitors, page views, average time on website, bounce rates or access paths. These will be collected for all elements of the e-mental health interventions (self-test, interactive online intervention, information about support services).

Further evaluation steps refer solely to the interactive online intervention. For an overview of the entire project please see Fig. 1.

**Fig. 1 Fig1:**
[figure not shown]
Overview of the project process

### Study design

The evaluation of the interactive online intervention draws on the evaluation, lessons and evidence of *The Ripple Effect* [31]. A mixed methods design with three measurement points will be realized. Prior to commencing the interactive online intervention (t_0_), sociodemographic and clinical data, attitudes and knowledge on suicidality (SOSS-SF and LOSS-SF) are collected. An interval-scaled questionnaire will also be developed—based on Bandura’s self-efficacy concept [58, 59]—to assess self-efficacy expectations when dealing with psychologically difficult situations. Psychometric properties of the new survey instrument will be described using the intervention sample. On completion of the intervention (t_1_), a post-survey will be conducted using SOSS-SF and LOSS-SF again (interval between t_0_ and t_1_ is dependent on the time participants take to complete the intervention). At a third time point (t_2_) (12–26 weeks after completion of the intervention), follow-up telephone interviews will be conducted with ten participants who agree to participate in a semi-structured telephone interview.

Due to the exploratory nature of the survey (first use of the intervention and survey tools in the German-speaking region) and the aim to allow participation from all interested persons, we decided against a randomised controlled design. The influence of the intervention on stigma and knowledge is examined, with a pre-post-design, according to the Australian example [31]. Further, qualitative information (e.g. individual experiences with the intervention) will be gathered in free-text fields as well as in follow-up interviews.

### Study sample: inclusion and exclusion criteria

Target group are adults (18 years or older) who have been affected by suicidality themselves or as close persons of those affected. Other interested people can participate as well. The nature of suicide experience is asked at the beginning of the intervention and is considered in the analysis.

In order to participate in the intervention, participants need internet access. Due to the fact that the materials are written in German, people who do not speak or understand the German language will be excluded.

### Acquisition of participants

Participants will be recruited via the e-mental health portal *psychenet.de* [36]. The portal has approximately 80,000 unique visitors per month. In a previous online survey, more than two thirds of users evaluated the *psychenet* website as good or very good [38]. Persons identified as having suicidal thoughts via the PHQ-9 [39] will receive information about their personal risk, support services and about the interactive online intervention (provided free of charge on a subdomain of *psychenet.de*)*.* The interactive online intervention and linked study will be promoted across several areas of the portal (e.g. homepage, disease-specific fact sheets, help section).

### Sample size calculation

As for *The Ripple Effect* [31], a conservative power calculation was performed (not accounting for repeated measures). In a pre-post comparison a sample size of *N* = 241 will be necessary to identify an effect size of d = 0.20 with a power of 0.80 and a significance level of α = 0.05 (dependent t-test, alpha adjusted for two endpoints: SOSS-SF and LOSS-SF). Assuming a dropout rate of 30%, a sample of *N* = 344 is needed at the beginning of the intervention (t_0_).

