The project is focused on the following aims:*To realize a representative population survey of knowledge and attitudes towards suicidality in Germany:* Knowledge about causes, signs, support, and treatment options of suicidality as well as attitudes towards suicidal persons (stigma) will be evaluated in order to deduce knowledge gaps and stigmatizing attitudes which can be addressed by the e-mental health interventions.*To develop e-mental health interventions:* Two e-mental health interventions will be developed: (a) an extension of the existing e-mental health portal psychenet.de focused on suicidality, and (b) an interactive online intervention focused on reducing suicide stigma, which will be available on a subdomain of *psychenet.de*. Evidence-based health information about suicidality and information on regional support services for severe mental or suicidal crises will be developed for both. One item assessing suicidal thoughts will be added to the existing self-test for depressive disorders (PHQ-9 [39]) and will be uploaded on *psychenet.de*. The interactive online intervention, inspired by the Australian project *The Ripple Effect* [31, 40], will consist of reports by persons with an experience of suicide in the form of 10–20 videos (duration: 2–5 min) and written experience reports. Psychoeducative elements and strategies to deal with suicide stigma will be developed for different target groups.*To evaluate the e-mental health interventions:* For evaluating the extension of the existing e-mental health portal *psychenet.de* (a) we will use web analytics. For evaluating the online intervention (b), participants will be recruited via *psychenet.de*. In a pre-post survey, we will evaluate to what extent an interactive online intervention reduces self-stigma and perceived-stigma, improves suicide literacy, self-efficacy expectations, and affects the participants’ intention to seek help (outcome evaluation). The participants’ evaluation of the content of the online intervention (e.g. satisfaction, helpful aspects) will also be assessed immediately after completing the intervention, as well as in a follow-up survey 12–26 weeks after completing the intervention (process evaluation). While the pre-post survey will primarily collect quantitative data, the follow-up survey will provide qualitative data by semi-structured telephone interviews.

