### Outcome measures

#### Primary outcome measures

Primary outcome measures will be change in suicide stigma and suicide literacy, measured quantitatively using the validated assessment tools SOSS-SF [46] and LOSS-SF [42] (pre- and post-completion of the online intervention).

Similar to *The Ripple Effect* [31], we will adapt the SOSS-SF from a general measure of suicide stigma to assess (1) negative attitudes towards oneself because of own suicidality (self-stigma), and (2) thoughts about how others think of suicidal persons (perceived-stigma).

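### Alpha and N are set for two endpoints, but the primary SOSS-SF is split into two unranked constructs and the analysis section drops the alpha adjustment

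*Protocol article*

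**What the plan says.** All references are to the protocol article, Aim 3 unless stated.

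- **Sample size calculation.** The study is sized "to identify an effect size of d = 0.20" "with a power of 0.80 and a significance level of α = 0.05", and "a sample size of *N* = 241 will be necessary". The test is a "dependent t-test, alpha adjusted for two endpoints: SOSS-SF and LOSS-SF". With 30% dropout this becomes 344 at t0.
- **Primary outcome measures.** Two outcomes are named, suicide stigma (SOSS-SF) and suicide literacy (LOSS-SF). The SOSS-SF is then to be adapted from a general measure to cover two numbered targets: "1) negative attitudes towards oneself because of own suicidality (self-stigma), and (2) thoughts about how others think of suicidal persons (perceived-stigma". Nothing says whether these form one score, are tested separately, or are ordered.
- **Secondary outcome measures.** Only self-efficacy and satisfaction are listed. Neither stigma version is placed here.
- **Study aims.** The pre-post survey asks how far the intervention "reduces self-stigma and perceived-stigma, improves suicide literacy", among other targets.
- **Statistical analysis.** Paired t-tests are planned for three scales, namely SOSS-SF, LOSS-SF and the self-efficacy scale. A significance threshold of 0.05 is applied to every analysis, with no mention of the adjustment.
- **Study sample.** Close persons of those affected and people with a general interest may enrol alongside people who have been suicidal themselves.

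**The concern.** The sponsor chose to adjust alpha for its primary endpoints, and N follows from that choice. An adjustment protects the conclusion only if it covers every primary test and is carried into the analysis. Here the count of endpoints is two in one section, while the primary stigma measure yields two results in the next. The analysis section then states a level that matches neither.

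With two stigma results and no rule, the one reported as the SOSS-SF endpoint could be chosen after the data are seen. The Discussion makes keeping the intervention online conditional on its meeting its aims, so the rule for success has a practical consequence.

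**Working it through.** **Inputs.** From Sample size calculation: d = 0.20, power 0.80, overall alpha 0.05, two endpoints, 30% dropout. The adjustment method and sidedness are not stated. A Bonferroni split with two-sided tests is inferred because it reproduces N.

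**Formula.** Paired t-test with n pairs: T has a noncentral t distribution with n − 1 degrees of freedom and noncentrality d√n. Power = P(T > t*) + P(T < −t*), where t* is the 1 − α/2 quantile of the central t. At n = 241 the noncentrality is 0.20 × √241 = 3.10.

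**1. The plan's own figure.** α = 0.05/2 = 0.025, two-sided: the smallest n with at least 80% power is 241, with power 80.15%. Dropout: 241/0.7 = 344.3, which is the stated 344 by rounding. Two-sided 0.05 without adjustment would have needed only 199, so a two-way split was used.

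**2. Three tests, error rate.** The upper bound is kα. The value under independence is 1 − (1 − α)^k.

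| Tests | Level per test | Upper bound | If independent |
|---|---|---|---|
| 2 | 0.025 | 5.0% | 4.9% |
| 3 | 0.025 | 7.5% | 7.3% |
| 2 | 0.05 | 10.0% | 9.75% |
| 3 | 0.05 | 15.0% | 14.3% |

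The last two rows use the level in the Statistical analysis section. Even with only two primary tests, that level does not hold 5%.

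**3. Three tests, power with the error rate held at 5%.** α = 0.05/3 = 0.0167, two-sided:

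- power at 241 pairs: 75.6%, a loss of 80.15 − 75.6 = about 4.6 points;
- effect detectable with 80% power at 241: d = 0.21;
- pairs needed for 80% power at d = 0.20: 265, which is 265 − 241 = 24 more; at t0, 265/0.7 = 378.6, so 379.

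**4. Number answering the self-stigma version.** It concerns the respondent's own suicidality. If only affected people answer it, n is below 241. Their share is not given, so the range is an assumption:

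| Assumed share of 241 | n | Power at 0.025 | Power at 0.05/3 |
|---|---|---|---|
| 25% | 60 | 23% | 19% |
| 50% | 120 | 47% | 41% |
| 75% | 181 | 67% | 61% |
| 100% | 241 | 80% | 76% |

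**The case against.** A reader might infer that the protocol runs three primary tests and that N = 241 is therefore wrong. The text does not support that. The sample size, primary outcome and analysis sections each count the SOSS-SF once, and the third scale in the analysis section is the secondary self-efficacy measure. The aims sentence also lists self-efficacy and help-seeking intention, so being named there does not make a construct primary. N = 241 contains no calculation error. If three tests were each run at 0.025, power per test would stay at 80% and only the familywise error would rise. All of this stands, and the three-test figures are therefore conditional.

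It can also be said that a condensed article may leave the handling of the two versions to a fuller document. That is fair as to scoring detail. It does not remove the mismatch in the printed text: an adjustment for two endpoints, a primary measure split in two, and a blanket 0.05. The readings that would rescue the two-endpoint count, a combined score or one version ranked first, are not written in the article.

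Finally, the study is uncontrolled and described as exploratory, the article itself disclaims causal attribution, and the sizing is called conservative for ignoring repeated measures. If d was meant on the raw-score scale (an assumption), power at 241 and 0.05/3 would run from 66% to 94% for pre-post correlations of 0.4 to 0.7. A loss of 4.6 points is small beside that. This limits the weight of the point. The mismatch itself remains.

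**Conclusion.** The point holds as an internal inconsistency of modest size. The endpoint count behind alpha and N is not secured by the definition of the primary stigma outcome, and the analysis section discards the adjustment that the sizing relies on.

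If self-stigma, perceived-stigma and literacy are each tested as primary, 5% familywise error and 80% power for each endpoint cannot both hold at 241 under a Bonferroni-type split. Either the error rate reaches up to 7.5% (15% at the level printed for the analysis), or power is about 76%. The second problem does not depend on the three-test reading: at 0.05 per test, two primary tests already allow up to 10%.

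These results assume two-sided tests, d as the standardised paired difference, and 241 completers on each measure. The last assumption is the weakest for self-stigma, where the loss could be far larger than 4.6 points.

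**What to change.** Make Sample size calculation, Primary outcome measures and Statistical analysis agree, in one of two ways.

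- **(a)** Name one SOSS-SF version as the primary stigma endpoint and make the other secondary. Test that version and the LOSS-SF at 0.025 each, or by Holm at an overall 0.05. N = 241 stays.
- **(b)** Declare three primary endpoints, test them by Holm at an overall 0.05, and restate power at 241 as about 76% per endpoint for d = 0.20 at the strictest step.

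In both cases, replace the blanket 0.05 for the primary tests and say who answers the self-stigma version. If only people with their own suicidality answer it, give its expected n and restate its power. Under (a), perceived-stigma is then the version that keeps the stated 80%. Under (b), the 76% does not apply to self-stigma.

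The cost is wording in three sections. Option (a) needs no extra participants if the chosen version is answered by all completers. Option (b) lowers the stated power by about 4.6 points, or needs 265 completers (379 at t0) to keep 80% for endpoints answered by all completers.

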### Outcome measures

#### Primary outcome measures

Primary outcome measures will be change in suicide stigma and suicide literacy, measured quantitatively using the validated assessment tools SOSS-SF [46] and LOSS-SF [42] (pre- and post-completion of the online intervention).

Similar to *The Ripple Effect* [31], we will adapt the SOSS-SF from a general measure of suicide stigma to assess (1) negative attitudes towards oneself because of own suicidality (self-stigma), and (2) thoughts about how others think of suicidal persons (perceived-stigma).

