Additionally, we used the short form of the Stigma of Suicide Scale (SOSS-SF) [46]. The SOSS-SF comprises 16 descriptors of a “typical” person who dies by suicide, covering three factors: ‘stigma’, ‘isolation/depression’, and ‘glorification/normalization’. Participants state on a 5-point Likert scale (strongly disagree, disagree, neutral, agree, strongly agree) to what extent they agree with the attributing descriptor (e.g. ‘brave’, ‘isolated’, ‘stupid’). Since the whole questionnaire in this study focused on persons with suicidal thoughts, we modified the original wording from “people who commit suicide” to “people who have suicidal thoughts”.

Additionally, we collected the socio-demographic variables age, gender, education and occupational status as well as religious denomination.

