### Strengths and limitations

#### Nationwide telephone survey

Telephone surveying has the benefit of accessing a large sample in an efficient manner. Further, the use of the Kish selection grid (to select a random person in households with several residents) and the computer-generated telephone numbers ensure that the sample is drawn from all persons with a telephone. The large number of participants and the representativeness of the sample allow a reliable estimation of the current knowledge and attitudes concerning suicidality in the German population. Thus, content and material of the online intervention can be adapted precisely.

The SOSS-SF and the LOSS-SF are tools to measure suicide stigma and suicide literacy. Since there are no validated instruments measuring suicide stigma and suicide literacy in German, they were translated, culturally adapted, and applied for the first time in the European region. Further, the instruments were used for the first time with a representative sample and via telephone.

As the survey is conducted in Germany, conclusions can only be drawn for the German speaking residential population and data cannot be generalized to other countries. Because suicidality is a very sensitive and taboo topic and telephone interviews may be considered impersonal, socially desirable answers are possible. Further, we cannot rule out a selection bias due to the exclusion of persons with neither a landline nor a cell phone—although the proportion of households with telephone in Germany is high (90.9% landline, 95,5% cell phone [60]).

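### Alpha and power are set for two primary endpoints, but the SOSS-SF is split into two stigma measures, which makes three primary scores, and the analysis section drops the alpha split

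*Protocol article*

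**What the plan says.** All places are in the protocol article, Aim 3 unless noted.

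- **Sample size calculation.** The basis is a "dependent t-test, alpha adjusted for two endpoints: SOSS-SF and LOSS-SF". With "a significance level of α = 0.05", a sample of "241 will be necessary to identify an effect size of d = 0.20 with a power of 0.80". A dropout of 30% raises this to 344 at t0.
- **Primary outcome measures.** Change in suicide stigma (SOSS-SF) and in suicide literacy (LOSS-SF) is primary. The SOSS-SF is then to be adapted to assess two things. The first is self-stigma, defined through the respondent's own suicidality. The second is listed as "2) thoughts about how others think of suicidal persons (perceived-stigma".
- **Background, Study aims, Discussion.** The Background defines self-stigma and perceived stigma separately. The Study aims, the abstract and the Discussion name both as targets.
- **Statistical analysis.** Paired t-tests are planned for SOSS-SF, LOSS-SF and self-efficacy, counted as three scales, so the SOSS-SF counts once. The significance level is 0.05 for every analysis. The section does not repeat the adjusted level, and does not say how the two SOSS-SF versions relate to the single SOSS-SF share of alpha.
- **Study sample.** Affected adults, persons close to them and anyone else interested may take part.

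**The concern.** The alpha adjustment and the power figure rest on a count of two, with the SOSS-SF counted once. The primary outcome definition turns that one entry into two measures of different constructs. If both are tested, as the aims suggest, the split is too generous for three tests and the stated power is too high. The analysis section goes further: read literally, its single level of 0.05 removes even the two-way split.

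At stake is the meaning of a significant stigma result. With no stated rule for which version carries the SOSS-SF share of alpha, that choice could be made after the data are seen. The Discussion makes continued availability of the intervention depend on its showing that it meets its aims, so the result has a practical use.

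There is also a question of who supplies data. Self-stigma because of one's own suicidality does not plainly apply to a bereaved relative or an interested reader, yet both count towards the 241.

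**Working it through.** **Inputs.** d = 0.20, power 0.80, overall alpha 0.05, two endpoints, 241 completers, 30% dropout (all from Sample size calculation). Assumptions: two-sided tests, since sidedness is not printed, and d taken as mean change divided by the SD of change.

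**1. The plan's own figure.** Paired t-test power is P(|T| > t(1−α/2; n−1)), with T noncentral t on n−1 degrees of freedom and noncentrality d√n.

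- α = 0.05/2 = 0.025 and n = 241: noncentrality 0.20 × √241 = 3.105, power 0.8015. The smallest n reaching 0.80 is 241.
- Normal approximation as a check: ((2.241 + 0.842)/0.20)² = 237.6, so 238.
- Without adjustment (α = 0.05), n would be 199.
- Dropout: 241/0.70 = 344.3, which matches 344 (345 if rounded up).

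The arithmetic is therefore right for two endpoints at two-sided 0.025 each.

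**2. Count of primary scores.** SOSS-SF self-stigma + SOSS-SF perceived stigma + LOSS-SF = 3.

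**3. Family-wise error.** The upper bound is kα; under independence it is 1 − (1 − α)^k.

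| Level per test | 2 tests: bound (independent) | 3 tests: bound (independent) |
|---|---|---|
| 0.025 | 5% (4.9%) | 7.5% (7.3%) |
| 0.05 | 10% (9.75%) | 15% (14.3%) |

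The second row is what the Statistical analysis section literally allows. It breaks the intended 5% even with two tests.

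**4. Power with a correct split over three.** α = 0.05/3 = 0.0167. Power at n = 241 is 0.756. The smallest n reaching 0.80 is 265, which is 265/0.70 = 378.6, or 379, at t0.

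**5. Self-stigma if only affected persons can answer it.** The article gives no share of affected persons, so a range is assumed.

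| Assumed share of 241 | Completers | Power at 0.025 | Power at 0.0167 |
|---|---|---|---|
| 25% | 60 | 0.23 | 0.19 |
| 50% | 120 | 0.47 | 0.41 |
| 75% | 181 | 0.67 | 0.61 |

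Under these shares, the reduced number of respondents costs much more power than the third test does.

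**The case against.** The strongest defence is that the article names the same two instruments in its sample size, primary outcome and analysis sections. It never says outright that both SOSS-SF versions will be tested as primary, nor that every participant answers both. Scoring and administration are details that an article may leave to the full protocol or SAP. The study is also declared exploratory and uncontrolled, the article itself disclaims causal attribution, and the loss from 0.80 to 0.756 is modest.

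Part of this stands. Missing scoring detail alone would be no finding, and the exploratory setting limits the consequences. But the article itself fixes the endpoint count, the alpha adjustment and N, and that count does not fit its own primary outcome definition. A later document could resolve this only by ranking or combining the two versions, and the article states neither.

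Some stronger readings are tempting but not supported:

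- **Seven tests.** A reader might take the Aim 1 Measures section, where the SOSS-SF describes a typical "person who dies by suicide, covering three factors", and infer 2 × 3 + 1 = 7 primary tests. That text describes the instrument as used in the telephone survey. Nothing in Aim 3 plans tests by factor, and nothing makes any one factor the required primary score.
- **Opposite movements.** A reader might infer from Strengths and limitations that self-stigma and perceived stigma are expected to diverge. That paragraph asks whether answering stigma scales may itself reinforce stigma, and both worries it raises point towards worsening.
- **Invalid instruments.** The outcome is "measured quantitatively using the validated assessment tools SOSS-SF [46] and LOSS-SF [42", while the telephone survey limitations begin "Since there are no validated instruments measuring suicide stigma and suicide literacy in German". The wording is uneven, but translation and adaptation are disclosed, and it has no bearing on alpha or power.

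**Conclusion.** The point holds: three primary scores stand against a two-way alpha split, and the analysis section then omits the split. The 241 is correctly calculated for two endpoints; the mismatch lies in the count and in who can answer.

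For three tests, family-wise error is at most 7.5% at 0.025 each and at most 15% at 0.05 each. With Bonferroni, power at 241 is 0.756. These figures assume two-sided paired t-tests, d = 0.20 for each score, and all 241 completers answering each one. The last assumption is doubtful for self-stigma, where power could lie anywhere from about 0.19 to 0.61 at 0.0167 over the assumed shares of 25% to 75%. The multiplicity effect alone is moderate. The possible loss for self-stigma is large, but depends on a share that the article does not give.

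**What to change.** Change the wording in Sample size calculation, Primary outcome measures and Statistical analysis so that they agree. Either option works without enrolling more people.

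- **Option A, two primaries.** Name one SOSS-SF version and one score from it as the primary stigma endpoint, make the other version secondary, and keep the two-way split. N = 241 then holds only if all completers can answer the chosen version. If self-stigma is chosen, state its power for the expected number of affected completers.
- **Option B, three primaries.** Declare self-stigma, perceived stigma and LOSS-SF primary and test them with Holm. Restate power as about 0.76 at 241 for scores that all completers answer. This is the Bonferroni figure, and Holm rejects whatever Bonferroni rejects. State self-stigma power separately for affected completers.

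In both options, replace the blanket 0.05 with the adjusted level or procedure for the primary tests, and fix the choice before outcome data are examined. As a minor point, describe the instruments in Primary outcome measures as translated and adapted, in line with the limitations section.

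The cost is text edits. Option B also means a lower stated power, and either option means a lower one for self-stigma where it is primary and not all completers can answer it.
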